### **3.9 Blinding**

Blinding of patients and investigators is not feasible. Data analysts will be blinded to the enrolment period.

### **3.10 Data Collection Methods**

Upon obtaining consent, the Research Assistant will assign a research subject ID number to patients. Data collection for outcome measures will be mainly collected in hospital by the Research Coordinator (at SickKids) and Research Assistant at the other sites. Study PROMs have been carefully selected and prioritized, hence they are sufficiently brief to be administered at baseline, 6 months, 12 months, and 24 months.

Data collection will occur using iPads or hardcopy during visits in the waiting room before or after appointments. At home, patient-families can also fill in the surveys via the internet (RedCap) with a protected ID provided to them by the study staff or through an electronic copy that will be sent back to the research assistant. Online data collection methods have been articulated as more client-centered to the needs of patient families; their consent to participate is often conditional on this provision. Flexible methods of data collection will maximize diversity of respondents and maintain the involvement of vulnerable groups (such as low transportation access) in the trial.

Qualitative interviews will take place in person or over the telephone to maximize convenience for participants. Audio data from patient interviews will be recorded, transcribed verbatim and secured for anonymity.

### **3.11 Data Management**

Data collection will be conducted by dedicated Research Assistants at each site, and synthesized by the Research Coordinator at SickKids. A study database will be designed and maintained as a secure Research Electronic Data Capture [REDCap] database. All data collection forms will be uploaded onto REDCap. The data on the various forms will be linked by a unique research subject ID number. The Research Coordinator will extract study data from questionnaires via the REDCap interface to complete the study-specific data collection forms on REDCap. An external user interface will also be created on REDCap for parents who opt to complete the surveys online.

All personal identifying information will be removed from the electronic study database. A separate secure list of research subjects' names and contact information will be maintained in an excel file for the purpose of the follow-up telephone interviews. All study-related electronic data files will be password-protected and reside on the Hospital server. Only members of the research team will have access to the server study file location via password-protected SickKids computers.

De-identified, password-protected databases with questionnaire data will be transferred to ICES through a Virtual Private Network from Sickkids. However, each individual site in partnership with their satellite clinics (Hamilton Health Sciences & CHEO) will be responsible for sending OHIP numbers to ICES. ICES will develop a data-sharing agreement with each site prior to the data exchange; the "data covenantor"- an ICES designate with special authority who is named at the Office of the Information Privacy Commissioner in Ontario to perform these duties - will act as the recipient. Sites will have the option to explore other data transfer modalities including web-based collection or an encrypted transfer with identification keys separated and transferred separately.

Further anonymization of transcripts will change names and other indirectly identifying information of participants as appropriate. The information the interview participants provide will not be linked or connected to the PROM data or ICES health utilization data in any way.

### **3.12 Statistical Methods and Data Analysis**

#### **Primary Analyses**

- i) Service Delivery (Primary) Outcomes: The primary analysis will be a comparison of the prioritized service delivery outcomes (Coordination of Care Among Health Providers and Families, Coordination of Care Between Health Providers and Families, Utility of Follow-Up Planning Tools) as measured with the FECC between the intervention and wait-list groups at the end of Year 1 (Month 12).
- ii) Scoring Requisites: The Coordination of Care outcomes (among providers and between providers and families) are 'dependency' questions that need to be endorsed in order for the outcome to be assigned a score >0. Where a prior question limits a following question from being visible, the answer to the following question will be

considered the lowest level of care (0). For example, if the parent answers no to “Did the main provider/team help you to manage your child's care or treatment from these different doctors or care providers?” (Q3a), the answer to the following question “In the last 6 months, did the main provider/team seem informed and up-to-date about the care your child got from other providers?” (Q5a) was considered ‘No’ (0).

- iii) Scoring: **Coordination of Care Among Health Providers** is based on the following questions in the FECC: Q5a, Q5b, and Q5d in FECC-8, with 3 possible responses that will be coded on an ordinal scale from 0 to 2, all of which are dependent on Q3a, response of ‘1’ indicating patient’s perception they have a care coordinator. All four questions will be added together to form an ordinal scale from 0 to 7 where larger values indicate better care. **Coordination of Care between Health Providers and Families** has four questions, Q9 and Q10 in FECC-5 with 4 possible responses that will be coded on a 0-3 ordinal scale, which are dependent upon Q3a (patient perception they have a care coordinator=1) and Q7 (care coordinator has initiated communication=1). All four questions will be added together to form an ordinal scale from 0 to 8, where larger values indicate better care. **Utility of Follow-Up Planning Tools** will be based on 2 questions on shared care plans (Q29 in FECC-16 and Q32 in FECC-17) with dichotomous responses (0 or 1) that added together, will create an ordinal scale from 0 to 2, where larger values indicate better care.

These scores will be used as three co-primary outcomes. The appropriate descriptive statistics will be used to compare groups with respect to baseline and demographic variables. Each outcome variable at Month 12 will be compared between groups using an ordinal regression incorporating center as a random intercept and adjusting for the baseline score. A two-sided test of hypothesis will be applied. The Holm-Bonferroni method will be used to deal with multiple testing (the three outcomes), where the overall target type I error rate is 0.05. The principle of intention-to-treat will be applied to the final analysis.

- iv) Child and Parent (Secondary) Outcomes: The data collection at 0 months and 6 months will be used to perform test-retest reliability, to establish baseline reference measures (0, 6, 12 months for this and other phases of intervention), and to assess for stability of outcome changes (24 months). Secondary child and parent outcomes will be compared at 0, 6 and 12 months using Bonferroni corrections to account for multiple testing. All secondary health system outcomes will be compared between the intervention and control as well.

- v) Process Outcomes: Process data collected through patient interviews will be first analyzed one participant at a time without making distinctions regarding the specific sample criteria articulated above. Following that, distinct issues brought forward for the specific sample criteria will be compared and contrasted to the main sample results. All interview data will be analyzed using a descriptive approach. The overarching themes will be selectively coded using the categories of ‘Active Ingredients’, ‘Fidelity’, ‘Dose’, and ‘Context’. The specific sub-themes under these pre-selected themes will be coded inductively.

- vi) Health System Outcomes: A cost comparison analysis will be performed as part of the primary analysis. Additionally, cost-effectiveness will be subsequently performed, expressed as an incremental cost-effectiveness ratio (ICER), calculated by dividing the incremental costs of the intervention by the incremental difference in hospitalization days during the study period as the primary analysis and an ICER denominated on emergency department visits as a secondary analysis. Direct health care costs will include cost of the CCKO intervention and health services use by participants during the 12 month follow up period. Health services use by participants and covered by the provincial payer will be obtained through administrative data from the linkage with ICES. This will be expressed as absolute difference between the two groups with a 95% confidence interval. An interview administered expense diary will capture indirect costs, parent out-of-pocket expenses and additional health services covered by third-party payers. Intervention costs will include all Health Human Resources required to execute the intervention and will be allocated evenly across all participants. Extensive sensitivity analysis will be used to test the robustness of the results and explore uncertainty in any of the underlying assumptions. Probabilistic sensitivity analyses (PSAs) will also be used to establish the point estimate and 95% confidence interval for the ICERs obtained. The time horizon for the primary analysis will be one year, bounded by the date of randomization and the one year follow up interview.

Additional Analyses:

- i) All analyses will be extended to 24 months to assess for any outcomes that may have delays in change and to assess for ongoing effects in enrolled subjects. All primary and secondary analyses will be conducted for Year 2 of the study comparing outcomes among patients in the two groups that they were assigned to.
- ii) Comparison of PROMs and Interview Data: Qualitative interview data will be compared with PROMs to ascertain the association between experience-related themes and specific health outcome measures. Data on PROMs will be stratified based on scores for different outcomes, and compared with the qualitative data to gain a better understanding of how families' experiences with the intervention mapped on to patients' health-related outcomes.
- iii) Sensitivity analysis #1: a) In order to address potential bias resulting from delays in initiation of complex care coordination after randomization, the primary analysis will be repeated using the initial complex care clinic visit date as the start of the intervention until 12 months from that date. b) To further explore this issue, an additional analysis will be performed through observation of the second year of outcome data post-randomization, using data from ICES. The comparison of Year 1 and Year 2 data will explore differences that may exist (in terms of group differences) and is expected to signal the importance of sensitivity analysis #1.
- iv) Sensitivity analysis #2: To account for health systems changes due to COVID-19 restrictions, which impacted most health service delivery across the country beginning March 13, 2020, an additional cost-effectiveness analysis will be conducted. For this analysis all health

service data collection will be truncated as of March 13, 2020 and the ICER will be calculated including health services use up to that date.

- v) Sensitivity analysis #3: Since health care utilization and costing data are being presented as per patient per year, in order to account for the small number of anticipated patients who may die or lose health insurance (OHIP) eligibility during the study, we will rerun the analyses excluding these patients. If this substantially changes study findings, data will be presented as per patient per month.
- vi) Health Services Use Among Patients excluded from RCT: A secondary analysis will be performed after completion of the primary trial analysis for children who were excluded from randomization (e.g. those judged to urgently need care coordination), as well as those who cannot complete questionnaires (non-English speaking patients). For such children, we will try to find age- and sex-matched controls in the catchment area of London Health Sciences Centre (where there is no complex care program) with similar patterns of health utilization in the year prior to enrolment and meeting criteria for CMC using an administrative database definition that we have used previously. We will employ a differences-in-differences approach comparing changes in health services utilization and cost, patient- (or caregiver-) reported health-related quality of life, and family functioning, for all children before- and after- intervention, controlling for time trends. Other analyses will also determine which predictor variables distinguish trajectories for at risk groups for future work.
- vii) In addition to a complete case analysis, since it was noted on original analysis that there was substantial missing data, the data were analyzed imputing missing values. Missing primary and secondary outcome data were imputed using multiple imputation by chained equations incorporating baseline variables, group assignment and the corresponding outcomes at baseline and 6 months.

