## **2.3 Trial Design**

CCKO will utilize a wait-list variation of a randomized controlled trial design (**Figure 1**). The wait-list approach involves rolling out an intervention over time, whereby all participants are randomized into two groups (A and B) to receive the intervention at different time points determined at random (22,23). Group A would receive the intervention immediately (when resources become available; at time 0). Group B would be on the wait-list and receive the intervention after 12 months. This study design uses the time period before the intervention as the control period/baseline, to be compared in parallel to those receiving the intervention (22). Baseline measurements would be collected at month 0, and Groups A and B would be compared at months 6 and 12.

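### Secondary outcomes: Month 0 is counted among the Bonferroni-corrected comparisons, against the trial design, and test-retest reliability is taken over an interval in which one arm is treated

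*Protocol*

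**What the plan says.** Protocol section 3.12, item iv (Child and Parent Outcomes), makes two statements that matter here.

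- On comparisons: "Secondary child and parent outcomes will be compared at 0, 6 and 12 months using Bonferroni corrections to account for multiple testing". The next sentence reads: "All secondary health system outcomes will be compared between the intervention and control as well". The closing words of that second sentence suggest that the first is also a comparison between arms. The size of the Bonferroni family is not given.
- On reliability: "The data collection at 0 months and 6 months will be used to perform test-retest reliability". No restriction to one arm, or to participants whose condition is unchanged, is stated.

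Other parts of the protocol bear on both.

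- Section 2.3 fixes the role of the visits: "Baseline measurements would be collected at month 0, and Groups A and B would be compared at months 6 and 12".
- Section 2.3 also fixes when treatment starts. For the first group: "Group A would receive the intervention immediately (when resources become available; at time 0". For the second: "Group B would be on the wait-list and receive the intervention after 12 months".
- Section 3.12, in the co-primary analysis, deals with baseline separately: "The appropriate descriptive statistics will be used to compare groups with respect to baseline and demographic variables".

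**The concern.** A correction for multiple testing implies tests. If Month 0 is one of three tested visits, a third of the secondary tests address a time before any intervention. A significant result there says nothing about treatment, and a null result is not informative about it either, but each such test tightens the threshold for the Month 6 and Month 12 comparisons. Those later comparisons carry the hypotheses on quality of life and parental fatigue in section 2.2.

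Test-retest reliability assumes that the thing measured has not changed between the two administrations. Here the trial hypothesizes change in half the sample over exactly the interval chosen. A pooled coefficient would treat a real response to care coordination as measurement error, and would make a scale look less reliable the more it responded.

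**Working it through.** **1. The plan's own figure.** Section 3.6 gives two-sided 5%, 80% power, a difference of 0.5 SD and 10% loss to follow-up, with 140 in total (70 per arm). By the normal approximation, n = 2(1.960 + 0.842)² / 0.5² = 62.8, so 63 per arm; 63 / 0.9 = 70 per arm, 140 in total. The figure reproduces. Power at 63 per arm for a single 5% test is 80.1% by the normal approximation and 79.5% by the t-test.

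**2. Cost of the Month 0 tests.** Inputs:

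- 63 evaluable per arm, from section 3.6 after 10% loss.
- An effect of 0.5 SD. This is an assumption: section 3.6 does not tie it to the secondary scales.
- The family. Section 3.4 lists two child outcomes (items 4 and 5) and four parent outcomes (items 6 to 9), six in all. Counting instruments gives eight: child KIDSCREEN, pain VAS, SWLS, parent KIDSCREEN, three PROMIS forms and the Expense Diary. A correction within each outcome is a third possible reading.

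The threshold is 0.05 / (outcomes × visits). Power is that of the two-sided two-sample t-test, with no baseline adjustment in the calculation.

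| Family | Tests with Month 0 | Threshold | Power | Tests without Month 0 | Threshold | Power | Difference |
|---|---|---|---|---|---|---|---|
| 8 instruments | 24 | 0.0021 | 37.2% | 16 | 0.0031 | 42.1% | 4.9 points |
| 6 listed outcomes | 18 | 0.0028 | 40.7% | 12 | 0.0042 | 45.8% | 5.1 points |
| Within each outcome | 3 | 0.0167 | 64.8% | 2 | 0.0250 | 70.4% | 5.6 points |

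The normal approximation gives levels one to two points higher and the same differences of about 5 points (39.3% to 44.1%, 42.7% to 47.7%, 66.0% to 71.4%).

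Month 0 is the smaller part of the loss. With eight instruments, power falls from 79.5% to 37.2%, which is 42.3 points, and Month 0 accounts for 4.9 of them. With six outcomes the fall is 79.5 − 40.7 = 38.8 points, of which 5.1 are due to Month 0. The rest comes from the number of outcomes and follow-up visits, which is not disputed here.

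**3. Effect on the reliability coefficient.** Take scores with unit variance and true reliability ρ. Let half the sample shift by d between Month 0 and Month 6, with individual responses varying by SD s. In large samples the absolute-agreement ICC is

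ICC = 2ρ / (var₀ + var₆ + Δ²),

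where var₀ = 1, var₆ = 1 + d²/4 + s²/2, and Δ = d/2 is the shift in the pooled mean. With d = 0.5, d²/4 = Δ² = 0.0625. All of ρ, d and s are assumptions.

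- ρ = 0.80, s = 0: 1.6 / 2.125 = 0.75
- ρ = 0.80, s = 0.5: 1.6 / 2.25 = 0.71
- ρ = 0.80, s = 1.0: 1.6 / 2.625 = 0.61
- ρ = 0.70, s = 0, 0.5, 1.0: 0.66, 0.62, 0.53
- Wait-list arm alone, no true change: 1.6 / 2 = 0.80, or 1.4 / 2 = 0.70

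Simulation of the same model gave the same values to within 0.002.

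**The case against.** **Month 0 may be loose drafting.** The sentence on secondary outcomes does not itself say that the comparison is between arms, and baseline variables are elsewhere to be compared descriptively. The wording could also describe a longitudinal comparison with Month 0 as the reference. This stands as a reason for caution: the between-arm reading rests on the sentence that follows. It does not remove the conflict with section 2.3, and text that allows both readings needs settling.

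**A Month 0 comparison has some use.** Section 3.3 has patients assigned before they are approached for consent, section 3.9 says blinding of patients is not feasible, and the timeline in section 3.5 allows consent at time 0. Baseline questionnaires may therefore follow allocation, and a look at Month 0 could reveal differential consent or reporting. That stands, but a descriptive table serves the purpose without a share of the divisor.

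**A reader might infer that the secondary outcomes will be analysed without baseline adjustment.** For the co-primary outcomes the protocol specifies a model, "using an ordinal regression incorporating center as a random intercept and adjusting for the baseline score", and for the secondary outcomes it names none. The silence does not support that inference. The secondary model is commonly left to a statistical analysis plan, which is not shown, and nothing in the protocol says that baseline will be ignored. Any power gain from adjustment would also rest on an assumed correlation between visits. It is not part of the loss counted above.

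**The reliability coefficient is peripheral.** No treatment estimate or hypothesis test in the protocol depends on it, and a uniform 0.5 SD shift moves it only from 0.80 to 0.75. Both observations are right. Nor does the protocol say that change over the first six months is to be relabelled as reliability; it says only that data from those two visits will be used for it. The defect is the missing restriction to untreated participants.

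**Conclusion.** The point holds on two limbs.

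First, section 3.12 and section 2.3 disagree on whether Month 0 is a compared visit. If it is tested between arms, it takes one third of the Bonferroni divisor and costs about 5 points of power for a 0.5 SD effect with 63 per arm. That difference is nearly the same under each reading of the family; the power level itself is not, and ranges from 37% to 65% with Month 0 included. It would be wrong to blame Month 0 for the whole distance from 80%.

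Second, test-retest reliability pooled over both arms would be understated if the intervention works. The direction follows from the design; the size depends on assumed values.

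The Month 0 error is conservative, and both limbs touch secondary analyses only. The co-primary comparison at Month 12 and its Holm-Bonferroni procedure are unaffected.

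**What to change.** - Reconcile section 3.12, item iv, with section 2.3: compare secondary child and parent outcomes between arms at Months 6 and 12 only, and present Month 0 descriptively.
- State the Bonferroni family explicitly, and count only the Month 6 and Month 12 tests in the divisor.
- Estimate agreement between Months 0 and 6 in the wait-list arm only, and call it stability. Six months is long to assume no true change, and section 3.4 itself expects that parents' and children's scoring may shift over time.
- As a recommendation and not a correction: adjust each secondary outcome for its own Month 0 value, as is already stated for the co-primary outcomes.

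The cost is one paragraph of text and no new data. The downside is that the stability estimate uses about half the sample and is less precise.

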### 3.6 Sample Size

For the RCT, we conservatively project the total sample size to be 140 (70/arm) based on the following criteria: i) Two-sided test of the null hypothesis at the 5% level; ii) Power of 80%; iii) 10% lost-to-follow-up; projected smallest clinically important difference of 0.5 of the within-patient standard deviation, which is recommended by the developer as a moderate effect size (39).

The required sample size is considered feasible as it is estimated that a pool of about 250 patients are readily identifiable for recruitment at CCKO sites.

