### **3.8 Randomization – Sequence Generation, Allocation Concealment and Implementation**

CCKO randomization will be done using a computer-generated algorithm. Eligible children will receive the intervention in either Time 1 (approximately Jan 2017) or Time 2 (approximately Jan 2018). Randomization will be stratified by region/centre. Blocking will be used to ensure that the two comparison groups are about the same size throughout the trial for each site as well as for the trial as a whole. An allocation ratio of 1:1 with random block sizes between 6 and 8 will be used within each stratum (centre). This will help to ensure that clinicians or investigators will not decipher the block size. After patient consent is obtained, the study investigator or his/her delegate will assign the patient a unique identification (ID) number in sequential order that will be used throughout the study.

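### Holm-Bonferroni, already used for the co-primary scores, could replace single-step Bonferroni for the secondary child and parent outcomes: same familywise guarantee, modest gain in power

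*Protocol*

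**What the plan says.** Protocol section 3.12 sets two multiplicity rules close together.

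- For the three co-primary FECC scores at Month 12 (item iii): "The Holm-Bonferroni method will be used to deal with multiple testing (the three outcomes), where the overall target type I error rate is 0.05".
- For the child and parent outcomes (item iv): "Secondary child and parent outcomes will be compared at 0, 6 and 12 months using Bonferroni corrections to account for multiple testing".

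Item iv gives neither the number of tests in the family nor its alpha level, and no reason for using a different procedure. Section 3.4 lists the outcomes: two for the child and four for the parent. They are measured with about eight instruments: KIDSCREEN Feelings, pain VAS, SWLS, the adapted KIDSCREEN for parents, PROMIS General Health, Sleep and Fatigue, and the Expense Diary.

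Section 3.6 powers the trial without reference to these outcomes. It sets out no power claim for them.

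**The concern.** Single-step Bonferroni compares every p-value with alpha/m. Holm compares the smallest with alpha/m, the next with alpha/(m-1), and so on, stopping at the first failure. Both keep the familywise error at or below alpha whatever the dependence between tests. Because no Holm threshold is below alpha/m, Holm rejects everything that Bonferroni rejects and sometimes more. On the familywise criterion, Bonferroni is therefore dominated for any family size.

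The plan already accepts Holm for the co-primary scores and then uses the less powerful procedure for a larger family. That family carries hypotheses ii) and iii) of section 2.2, on the quality of life of children and parents and on parental fatigue. These hypotheses expect several outcomes to improve together, which is the setting in which Holm gains most. At stake is some power on secondary outcomes. The primary analysis and the sample size are not affected.

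**Working it through.** **1. Reproduce the plan's own sample size.** Inputs from section 3.6: "Two-sided test of the null hypothesis at the 5% level", 80% power, "projected smallest clinically important difference of 0.5 of the within-patient standard deviation" and "10% lost-to-follow-up". Section 3.8 gives 1:1 allocation.

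n per arm = 2(1.960 + 0.842)² / 0.5² = 62.8, rounded up to 63. With 10% loss, 63/0.9 = 70 per arm, 140 in total. This matches the stated figure, so 63 evaluable per arm is the planned number.

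**2. Bonferroni power for one real effect.** Assume that the 0.5 SD also applies to a secondary outcome. The expected z is 0.5 × √(63/2) = 2.81. With m = 8 the two-sided threshold is 0.05/8 = 0.00625 (critical value 2.73), and power is 52.9%. For other family sizes:

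| m | threshold | power |
|---|---|---|
| 6 | 0.00833 | 56.7% |
| 8 | 0.00625 | 52.9% |
| 16 | 0.00313 | 44.1% |
| 24 | 0.00208 | 39.3% |

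The protocol does not state m. The range runs from 6 (six listed outcomes at one visit) to 24 (eight instruments at three visits).

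**3. Bonferroni against Holm by simulation.** Two-sided z-tests, 63 per arm, alpha 0.05. Effect size, correlation and share of real effects are assumptions, because the protocol gives none of them for these outcomes. Average power per real effect at 0.5 SD and correlation 0.4:

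| Family | Real effects | Bonferroni | Holm | Gain (points) |
|---|---|---|---|---|
| 8 | all 8 | 52.8% | 63.8% | 11.0 |
| 8 | 4 | 52.9% | 56.0% | 3.1 |
| 8 | 2 | | | about 1.0 |
| 8 | 1 | | | about 0 |
| 16 (months 6 and 12) | all 16 | 44.1% | 54.7% | 10.6 |
| 16 | 8 | 44.0% | 47.1% | 3.1 |
| 24 (with month 0) | 16 | 39.1% | 43.4% | 4.3 |
| 24 | 8 | | | about 1.7 |

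The last two rows take item iv literally. Month-0 comparisons precede any treatment effect and are true nulls under randomisation, so at most 16 of the 24 can be real.

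Correlations of 0 and 0.5 give a similar picture. For m from 6 to 24 the gain is about 0 points with one real effect, about 3 with half real, and about 7 to 12 with all real.

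**4. Smaller effects, 8 tests, correlation 0.4.** At 0.3 SD the gain is 2.9 points if all effects are real and 0.9 if half are. At 0.2 SD it is 0.8 and 0.3.

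**5. What does not change.** Holm's first step is the Bonferroni test, so the chance of at least one rejection is identical in every case. The chance of detecting all of the effects does change: with all eight real at 0.5 SD it is 9.4% under Bonferroni and 33.3% under Holm.

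**6. Realised familywise error.** With 8 tests, half of them real, at 0.5 SD and correlation 0.4, it is 0.023 for Bonferroni and 0.033 for Holm. Both are below 0.05.

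**The case against.** The strongest reply is that nothing is wrong. Bonferroni controls familywise error validly, a plan may use different procedures for different families, and these outcomes were never powered. All of that stands, and it is why the point is an optional improvement.

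Second, the largest gain needs every effect to be real and as large as 0.5 SD. That figure is the sample-size assumption; the protocol does not project it for pain, life satisfaction, PROMIS or expenses. This also stands. A reader might infer that true effects will be missed because of the correction, or that the loss is greatest in the largest family. The figures support neither: the gain can be close to zero, and it does not rise steadily with m.

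Third, a reader might infer that Bonferroni gives no gain in error control. That is too strong. Only the nominal familywise bound is the same. Bonferroni has the lower realised error when some effects are real, bounds the expected number of false rejections at alpha, and has simple matching simultaneous confidence intervals. Against this, the only error target stated in section 3.12 is an overall rate of 0.05, for the primaries, where Holm is accepted. The protocol promises no simultaneous intervals for the secondary outcomes.

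Fourth, the text does not say *single-step*, and details may sit in a SAP that is not shown. Single-step is still the natural reading, because the preceding item names Holm-Bonferroni where it means Holm.

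Fifth, timing. Additional Analyses item vii reports that substantial missing data were seen when the data were originally analysed, so this version was edited after an analysis. Switching at that stage to a rule that can only add rejections would look like a post-hoc relaxation. This stands and shapes the fix. The same item means that 63 evaluable per arm may be optimistic.

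**Conclusion.** The point holds as a modest efficiency gain. For the secondary child and parent outcomes the plan fixes a valid procedure that Holm dominates on the familywise criterion, although it uses Holm for the co-primaries.

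That dominance holds for any family size and any dependence. The size of the gain does not: the power figures rest on the planned 63 per arm and on assumed effects, correlations and family sizes. On those assumptions the gain at 0.5 SD with 8 tests runs from nothing to about 11 points per real effect, and it shrinks to a few points or less when effects are smaller or few are real.

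The documents do not support reading this as a contradiction, as a wrong figure, or as a threat to the trial's conclusions on its primary outcomes.

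**What to change.** In section 3.12 item iv, replace the reference to Bonferroni corrections with the Holm-Bonferroni method for the secondary child and parent family, and apply it to the post-baseline comparisons (months 6 and 12). Leaving month 0 out avoids spending alpha on comparisons that are null by design.

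Report Holm-adjusted p-values. If ordinary 95% confidence intervals stand beside them, label them as unadjusted, since an interval may exclude zero next to a non-significant adjusted p-value.

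If outcome data have already been analysed, report the Bonferroni result as well and say when the change was made.

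The cost is a short change of wording, a slightly higher realised familywise error (still at most 0.05), and the loss of simple matching simultaneous intervals. No extra participants or data are needed. Keeping Bonferroni would remain defensible.
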